| 
1) Primary Objective. To demonstrate that vaccination with a 3-dose regimen of 9vHPV will reduce viral infectivity in cervical, anal, urine, vulvar and oral samples from HPV 16/18/16+18-positive women.
 
Hypothesis. 9vHPV promotes the production and exudation of anti-HPV antibodies, which neutralize new HPV16/18 virions and reduce the infective capacity of body fluids in HPV-positive women and the transmission of HPV infection.
 | 
 
● In-vitro infectivity evaluation (by expression of E1^E4 HPV biomarker in HaCaT keratinocytes) of cervical, anal, urine, vulvar and oral samples collected before and after 9vHPV vaccination.
 
● Detection of HPV 6/11/16/18/31/33/45/52/58 L1 antibodies in cervical, anal, urine, vulvar and oral samples collected before and after 9vHPV vaccination, using             
 
– ELISA for types 16 and 18 in samples from RIFT-HPV 1 and 2 study cohorts,
 
– cLIA for all 9vHPV-covered types in samples from RIFT-HPV 1 study cohort.
 
 
This endpoint will allow associating the reduction in viral infectivity with the presence of neutralizing antibodies.
 
 
● HPV16/18 virion detection (using ELISA, electronic microscopy) and HPV DNA
 
 |

|                                                                                                                                                                                                                                                                                                                                                                                                                                                                                                                                           |                                                                                                                                                                                                                                                                                                                                                                                                                  |

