| Laboratory Procedures       | 
Analysis of E1E4 HPV biomarker expression in HaCaT keratinocytes in-vitro after exposure to cervical, anal, urine, vulvar or oral samples.
 
Detection of HPV16/18 in cervical, anal, urine, vulvar and oral samples, using ELISA/electron microscopy and HPV test/genotyping (Anyplex HPV28).
 
Detection and titration of anti-HPV 6/11/16/18/31/33/45/52/58 L1 antibodies in serum, cervical, anal, urine, vulvar and oral samples, using ELISA and cLIA.
 |
| Estimated Duration of Study | 2 years from the time the first subject signs the informed consent until the last subject's last study visit.                                                                                                                                                                                                                                                                                                                                                                                   |

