| Anal sample collection                                                                                                                         | ✓ | ✓ | ✓ | ✓ |
| First-void urine collection                                                                                                                    | ✓ | ✓ | ✓ | ✓ |
| Oral sample collection                                                                                                                         | ✓ | ✓ | ✓ | ✓ |
| Blood sample collection                                                                                                                        | ✓ | ✓ | ✓ | ✓ |
| Vaccination + 30 min monitoring for post-vaccination immediate adverse events                                                                  | ✓ | ✓ | ✓ |   |
| AE/SAE assessment                                                                                                                              |   | ✓ | ✓ | ✓ |
| Laboratory analytical procedures                                                                                                               |   |   |   |   |
| HPV infective capacity in-vitro evaluation (E1^E4-HaCaT model)                                                                                 | ✓ | ✓ | ✓ | ✓ |
| Anti-HPV 6/11/31/33/45/52/58 L1 ab detection/titration by cLIA in cervical, anal, oral, urine, vulvar and blood samples from RIFT/HPV 1 cohort | ✓ | ✓ | ✓ | ✓ |
| Anti-HPV 16/18 L1 ab detection/titration by ELISA in cervical, anal, oral, urine, vulvar and blood samples from RIFT/HPV 1 and 2 cohorts       | ✓ | ✓ | ✓ | ✓ |
| HPV test and genotyping (Anyplex HPV28) in cervical, anal, urine, vulvar and oral samples                                                      | ✓ | ✓ | ✓ | ✓ |

|                                                                                                            |   |   |   |   |
|------------------------------------------------------------------------------------------------------------|---|---|---|---|
| HPV16/18 virion detection (ELISA, electronic microscopy) in cervical, anal, urine, vulvar and oral samples | ✓ | ✓ | ✓ | ✓ |
|------------------------------------------------------------------------------------------------------------|---|---|---|---|

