| 
Hypothesis. 9vHPV promotes the production and exudation of anti-HPV antibodies, which neutralize new HPV16/18 virions and reduce the infective capacity of body fluids in HPV-positive women and the transmission of HPV infection.
                                                                                                                                                                                                                                                 | 
 
● Detection of HPV 6/11/16/18/31/33/45/52/58 L1 antibodies in cervical, anal, urine, vulvar and oral samples collected before and after 9vHPV vaccination, using             
 
– ELISA for types 16 and 18 in samples from RIFT-HPV 1 and 2 study cohorts,
 
– cLIA for all 9vHPV-covered types samples from RIFT-HPV 1 study cohort.
 
 
 
 
This endpoint will allow to associate the reduction in viral infectivity with the presence of neutralizing antibodies.
 
 
● HPV16/18 virion detection (using ELISA, electronic microscopy) and HPV DNA detection and genotyping (using Anyplex HPV28) in cervical, anal, urine, vulvar and oral samples collected before and after 9vHPV vaccination.
 
 
This endpoint will allow to identify samples of subjects with a non-productive viral infection or undergoing natural clearance, and distinguish them from samples of subjects with productive but reduced infection due to 9vHPV vaccination.
 |

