During Visit 1, eligibility criteria defined in section [5](#) will be reviewed with subjects after they read the Subject's Information Sheet and sign the Informed Consent Form (annex [11.2](#)). Those subjects complying with inclusion and exclusion criteria will be enrolled in the study and included in RIFT-HPV 1 or 2 study cohorts according to baseline characteristics.

All enrolled subjects will complete the specified procedures in 4 study visits: Visit 1/Day 1, Visit 2/Month 2, Visit 3/Month 6, and Visit 4/Month 7. Study procedures and time windows for each visit are summarized in the Schedule of Activities (section [1.2.2](#)).

9vHPV vaccine will be administered in Visits 1, 2 and 3 by a qualified health professional (Study nurse/Sub-Investigator).

There is no control group in this study: all subjects signing the Informed Consent Form will receive 9vHPV vaccination in a three-dose regimen as per protocol (section [8.1.9](#)) and therapeutic indication.

All enrolled subjects will follow the study procedures summarized below as per protocol (section [1.2.2](#)):

- Pregnancy test on a urine sample in Visits 1, 2, 3 and 4 before receiving any vaccine or collecting any sample.
- Completion of a questionnaire in Visits 1 and 4.
- Cervical, vulvar and anal sample collection by the study Investigator, and oral, urine and blood sample collection by the study nurse. All samples will be collected in Visits 1, 2 and 3 before receiving 9vHPV vaccination, and in Visit 4.
- Intramuscular administration of 9vHPV in a three-dose regimen in Visits 1, 2 and 3.

The following study laboratory procedures will be applied to samples obtained from study subjects:

- Assessment of HPV infectivity. Analysis of E1+E4 HPV biomarker expression in HaCaT keratinocytes in-vitro after exposure to cervical, anal, urine, vulvar or oral samples from all study subjects.
- Assessment of HPV positivity. Detection of HPV16 and 18 in cervical, anal, urine, vulvar and oral samples from all study subjects, using ELISA/electron microscopy to detect HPV virions, and HPV test/genotyping (Anyplex HPV28) to detect HPV DNA.
- Assessment of HPV immunogenicity. Detection and titration of anti-HPV L1 antibodies in serum, cervical, anal, urine, vulvar and oral samples from all study subjects, using ELISA for types 16 and 18 in samples from RIFT-HPV 1 and 2 study cohorts, or cLIA for all 9vHPV-covered types in samples from RIFT-HPV 1 study cohort.

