##### 9.1.1.1.2 *Inclusion in the analysis population*

The below criteria will be followed to include cases in the analysis population:

Before vaccination (Visit 1):

- HPV16/18/16+18 positive DNA detection and genotyping (using Anyplex HPV28) in collected cervical, anal, urine, vulvar and oral samples.
- HPV16/18 positive virion detection (using ELISA, electronic microscopy) in collected cervical, anal, urine, vulvar and oral samples.

Therefore, cases showing:

- negative HPV16/18 DNA test and/or
- absence of HPV16/18 viral particles,

will not be included in the analysis population.

After vaccination (Visits 2 to 4, Months 2, 6 and 7):

- HPV16/18/16+18 positive DNA detection and genotyping (using Anyplex HPV28) in collected cervical, anal, urine, vulvar and oral samples.
- HPV16/18 positive virion detection (using ELISA, electronic microscopy) in collected cervical, anal, urine, vulvar and oral samples.
- Positive detection of exudated HPV 6/11/16/18/31/33/45/52/58 L1 antibodies in collected cervical, anal, urine, vulvar and oral samples.
- Positive detection/titration of HPV 6/11/16/18/31/33/45/52/58 L1 antibodies in collected serum samples (positive seroconversion).

Therefore, cases showing:

- negative HPV16/18 DNA test and/or
- absence of HPV16/18 viral particles and/or

- absence of exudated HPV L1 antibodies and/or
- absence of positive seroconversion,

will not be included in the analysis population.

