### 9.1.4 Definitions Regarding Data Description and Analysis.

**Infectivity rate:** The infectivity rate of cervical, anal, urine, vulvar and oral samples collected from study subjects before and after 9vHPV vaccination will be obtained measuring the in-vitro expression of HPV biomarker E1E4 mRNA in HaCaT keratinocytes incubated during 24h with study samples (quantitative variable). The expression level of a positive control sample and the human gene HPRT1 will be used to normalize the expression measurements. The quantity of HPV-infected keratinocytes (i.e., expressing E1E4 mRNA) will be directly proportional to the quantity of free HPV viral particles present in samples (i.e. not neutralized by HPV antibodies). Reduction in infectivity will be expressed as the difference between the infectivity rate of cervical, anal, urine, vulvar and oral samples before and after the subject receives 9vHPV vaccination.

**HPV persistent infection:** an HPV infection of the same genotype and sample type (oral, anal, urine, vulvar or cervical) detected in samples collected at Day1/Visit 1 and Month 7/Visit 4 is defined as persistent infection (qualitative variable: persistent or non-persistent infection).

**HPV productive infection:** an HPV positive infection that produce new viral particles detected by immunoassays or EM in oral, anal, urine, vulvar or cervical samples is defined as productive infection (qualitative variable: presence or absence of viral particles).

**Positive/negative HPV seroconversion:** it is defined as the status of study serum samples regarding presence (positive) or absence (negative) of type-specific HPV antibodies. Positive seroconversion may occur after administration of study vaccine, or by subject's natural immunological response to a previous HPV infection. Negative seroconversion may occur when study vaccine fails to trigger an immunological response in the subject. Quantitative results of the HPV antibodies detection test are reported in terms of arbitrary units (milliMerck units/ml). Results may be reported qualitatively as positive or negative seroconversion for type-specific HPV antibodies.

**Anti-HPV antibodies exudation:** type-specific HPV antibodies will be detected in cervical, anal, urine, vulvar and oral samples (cLIA/ ELISA), and results will be expressed qualitatively as antibody presence or absence.

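### Mucosal antibody is scored only as present or absent, and the inclusion rule requires it to be present after vaccination, so the promised link between antibody and infectivity cannot be estimated from it

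*Protocol*

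**What the plan says.** Mucosal antibody is listed as an endpoint under the primary objective, with a stated purpose. Protocol Section 1.1.5: "This endpoint will allow associating the reduction in viral infectivity with the presence of neutralizing antibodies". Section 3 repeats it: "This endpoint will allow to associate the reduction in viral infectivity with the presence of neutralizing antibodies".

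Three places plan titration in mucosal samples as well as serum:
- Section 1.2.1, laboratory procedures: "Detection and titration of anti-HPV 6/11/16/18/31/33/45/52/58 L1 antibodies in serum, cervical, anal, urine, vulvar and oral samples, using ELISA and cLIA".
- Section 1.2.2, schedule of activities, ticked at all four visits: "Anti-HPV 16/18 L1 ab detection/titration by ELISA in cervical, anal, oral, urine, vulvar and blood samples from RIFT/HPV 1 and 2 cohorts".
- Section 4.1, list of laboratory procedures: "Detection and titration of anti-HPV L1 antibodies in serum, cervical, anal, urine, vulvar and oral samples from all study subjects".

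Section 9.1.4 fixes the form of the mucosal result: "results will be expressed qualitatively as antibody presence or absence". The entry just before it, on serum, keeps a quantitative result in milliMerck units/ml.

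Section 9.1.1.1.2 sets a condition for Visits 2 to 4: "Positive detection of exudated HPV 6/11/16/18/31/33/45/52/58 L1 antibodies in collected cervical, anal, urine, vulvar and oral samples". The matching list of cases left out of the analysis population includes "absence of exudated HPV L1 antibodies and/or". Section 9.1.2.2.1 applies the same inclusion criteria to the 1-dose and 2-dose analyses. Section 9.1.1.2 names a paired Wilcoxon signed rank test of infectivity, Visit 1 against Visit 4, with no antibody term.

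**The concern.** The trial has a single arm and no control, and Section 2.2.7 notes that most HPV infections clear within 12 to 24 months. A before/after fall in infectivity cannot by itself separate vaccine from time. A link between antibody at the mucosal site and loss of infectivity there is one of the few internal pieces of evidence that could help, and the protocol says this endpoint will supply it.

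Two of the protocol's own rules work against that. One discards the quantity of antibody at the sites where the hypothesis places neutralization. The other removes the women without antibody, who would have provided the contrast. This is not a detail left for a later analysis plan, since both rules are fixed in the protocol text.

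**Working it through.** **Step 1: the variable under the plan as written.** Let A1 and A4 be mucosal antibody at Visit 1 and Visit 4, each scored 0 (absent) or 1 (present) as Section 9.1.4 directs. Reading Section 9.1.1.1.2 sample by sample, A4 = 1 for every included case.
- Variance of A4 = p(1 − p) with p = 1, which is 0. A correlation with infectivity, or a present-versus-absent comparison, is undefined at any n.
- Within-woman change = A4 − A1 = 1 − A1. It carries nothing beyond Visit 1 status. A woman with natural mucosal antibody scores present at both visits, so any rise after vaccination cannot be seen in her.

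**Step 2: how far this depends on reading.** The rule lists nine types separated by slashes and does not say any or all. If any one type suffices, a woman may be included through another type while antibody matched to her infecting type is absent. Type-matched status could then vary a little, so the variable is nearly rather than strictly constant.

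**Step 3: what the cut costs once antibody-absent women are kept.** For a normally distributed log titre cut so that a fraction p is positive, the share of information kept is φ(c)² / [p(1 − p)], where c is the cut point:
- p = 0.90: 0.1755² / 0.09 = 0.34
- p = 0.95: 0.1031² / 0.0475 = 0.22

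**Step 4: illustrative power.** The protocol gives no figure for this association, so there is none to reproduce. Inputs:
- n = 39 (Section 9.2.1) and n = 28 (Section 9.2.2).
- n = 23, from 39 × (1 − 0.40) = 23.4, if the 40% loss in Section 9.2.1 falls on 39 enrolled women.
- 90% positive: the serum expectation in Section 9.1.2.1.2, assumed here for mucosa.
- True correlation 0.5: assumed.
- Two-sided 0.05.

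Simulation used 3,000 runs per setting with bivariate normal log titre and infectivity reduction. Titre was tested by Spearman and presence/absence by rank-sum. n is the number before any filter; at 90% positive the filter leaves about 39 × 0.9 = 35, 28 × 0.9 = 25 and 23 × 0.9 = 21 women.

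| Analysis | n = 39 | n = 28 | n = 23 |
|---|---|---|---|
| As written (binary, filter kept) | undefined | undefined | undefined |
| Binary, filter lifted | 0.39 | 0.25 | 0.21 |
| Titre, filter kept | 0.71 | 0.56 | 0.46 |
| Titre, filter lifted | 0.88 | 0.74 | 0.64 |

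In the second row, about 2%, 5% and 9% of runs had no antibody-absent woman and were counted as not significant. At 95% positive that row falls to 0.22, 0.14 and 0.10.

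**Step 5: the correlation detectable with both changes.** By Fisher's z at 80% power, r = tanh[(1.960 + 0.842) / √(n − 3)]:
- n = 39: tanh(2.802/6.00) = 0.44
- n = 28: tanh(2.802/5.00) = 0.51
- n = 23: tanh(2.802/4.47) = 0.56

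**The case against.** The best reply has five parts.

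1. **Titration is contested within the protocol.** The endpoint entries in Sections 1.1.5 and 3 say detection for mucosal samples and titration for serum. Sections 8.2.1.1 to 8.2.1.4 collect mucosal samples for antibody detection, Section 8.2.1.5 sends serum for titration, and Sections 8.2.2.3 and 8.2.2.4 describe antibody measurement in serum. Section 9.1.4 may simply follow the detection reading. This stands. A reader might infer from the schedule that a mucosal titre will certainly exist at no further cost, but the documents do not settle that.

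2. **A binary result may have an assay reason.** The specimens are a brush in 5 ml PBS, a 10 ml rinse, a dry swab and first-void urine, with no normaliser stated for antibody. Dilution can differ between visits and can move titre and infectivity together, since both come from the same sample. This stands as a limit on interpretation. The protocol does not offer it as a reason for the cut.

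3. **Other information survives.** Visit 1 mucosal status is unrestricted, serum antibody stays quantitative, and Section 9.1.1.2 plans a sensitivity analysis in women seronegative at baseline. All true, but the first two are indirect and the protocol plans no analysis relating them to infectivity. The sensitivity analysis would largely remove the Visit 1 contrast and still has no antibody term.

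4. **The endpoint promises association with the presence of antibody, not a dose-response.** Fair, but an association with presence needs some women in whom antibody is absent, and the inclusion rule removes them.

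5. **No present-versus-absent test is planned, and the association method could sit in a separate analysis plan.** This stands against treating the power figures as a measured loss. It does not rescue the endpoint, because an analysis plan that followed the protocol's two rules would still have a constant to work with.

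**Conclusion.** The point holds. As written, post-vaccination mucosal antibody is present by construction in the analysis population, or nearly so under the any-type reading. The association that Sections 1.1.5 and 3 promise therefore cannot be estimated from it after vaccination, including in the 1-dose and 2-dose analyses. This follows from the text and needs no assumption about effect size.

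Three stronger conclusions are tempting and not supported:
- **That 0.88 against 0.39 is the power the plan gives up.** Both figures require the inclusion filter to be lifted, so neither describes the plan as written. They also rest on an assumed correlation, a serum positivity rate carried over to mucosa, and sample sizes set for another comparison. The joint two-cohort analysis of cervical samples could give a larger n.
- **That rewording Section 9.1.4 alone repairs the endpoint.** With the filter kept, the titre is analysed over a truncated range in fewer women (0.71, 0.56 and 0.46).
- **That the primary result fails for this reason.** The paired test of infectivity can still be run. What is lost is the evidence on mechanism attached to it.

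This should be corrected before analysis.

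**What to change.** Both of the first two changes are needed.

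1. **Section 9.1.4:** analyse mucosal anti-HPV16/18 as log titre matched to the infecting type, with values below the assay limit set to one fixed, stated value. Keep presence/absence as a description.
2. **Section 9.1.1.1.2:** state that samples without mucosal antibody are not excluded from the analysis relating antibody to infectivity, and say whether the nine-type condition means any or all types wherever it still applies.
3. **Association analysis:** name a Spearman correlation of the within-woman, same-site change in log titre from Visit 1 to Visit 4 with the change in infectivity. A rank method tolerates undetectable Visit 4 values, which the hypothesis predicts.
4. **Reconcile the measurement text:** bring detection and titration (Sections 1.2.1, 1.2.2 and 4.1) into line with detection alone (Sections 1.1.5, 3 and 8.2.1.1 to 8.2.1.4), and with the serum-only descriptions in Sections 8.2.1.5, 8.2.2.3 and 8.2.2.4.

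Cost: wording in a few sections. If mucosal titration is carried out as Sections 1.2.1, 1.2.2 and 4.1 state, no extra visits, samples or assays are needed. If only detection was intended, the laboratory cost is open and has to be established. Within-woman change reduces dilution noise but does not remove it, so the association should be reported as supportive evidence.

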## 9.2 Sample Size and Power

### 9.2.1 RIFT-HPV 1 cohort

The sample size for this cohort has been calculated based on the demonstration of viral infectivity reduction before and after a 3-dose regimen of 9vHPV vaccination in cervical samples as a reference.

Accepting an alpha risk of 0.05 and a beta risk of less than 0.2 in a bilateral contrast, it has been estimated that a minimum of 39 women fulfilling the 3-dose vaccination schedule is needed to detect a difference equal to or greater than a 25% infectivity reduction in cervical samples.

It has been estimated a 40% sampling loss from those study subjects:

- showing an HPV16/18/double 16-18 positive result not confirmed by Anyplex HPV28,
- not fulfilling the 9vHPV 3-dose schedule,
- showing HPV clearance at Month 7 visit,
- showing a non-productive infection before vaccination.

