### 1.1.6 Study Population

A minimum of 39 and 30 subjects will be included in the RIFT-HPV 1 and 2 study cohorts respectively, according to inclusion and exclusion criteria described in section 5.

All study activities listed in section 1.2.2 will be performed on RIFT-HPV 1 and 2 cohorts.

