The analysis performed on anal, urine, vulvar and oral samples obtained from the combination of both study cohorts will increase the statistical power of the analysis performed in cervical samples. Moreover, results on the evaluation of the impact of HPV vaccination on infective capacity of the virions present in cervical, anal, urine, vulvar and oral samples may yield valuable information about HPV infectivity in different anatomical areas that are involved in the transmission process of the virus.

Therefore, this study's results can be the necessary proof-of-concept (i.e. HPV vaccination can reduce viral infectivity and prevent viral transmission) to generate scientific evidence that 1) may endorse HPV vaccination in adult women and promote the design of more effective population-based vaccination programs for preventing cervical cancer; 2) may open the door to additional studies of HPV infectivity and transmission on male and female populations, focused on the reduction of the incidence of non-cervical anogenital and oropharyngeal cancers.

The size of the study population was calculated using the primary endpoint (reduction of HPV infective capacity after 3 doses of 9vHPV) as a reference. Accepting an alpha risk of 0.05 and a beta risk of less than 0.2 in a bilateral contrast, it is estimated that a minimum of 39 and 28 subjects for the first and second study cohorts respectively should be included in the study.

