## 5.3 SUBJECT REPLACEMENT STRATEGY

A subject who discontinues from study vaccination or withdraws from the study will not be replaced.

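### RIFT-HPV 1 uses 39 both as the number of three-dose completers needed and as the number to enrol, with a stated 40% loss not carried through; read literally, power in that cohort is about 56–58%

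*Protocol*

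**What the plan says.** Section 9.2.1 sizes RIFT-HPV 1 on the cervical comparison before and after three doses. The error rates are "Accepting an alpha risk of 0.05 and a beta risk of less than 0.2 in a bilateral contrast". The requirement is a "minimum of 39 women fulfilling the 3-dose vaccination schedule is needed to detect a difference equal to or greater than a 25% infectivity reduction". Directly afterwards comes "It has been estimated a 40% sampling loss from those study subjects", followed by four reasons: HPV type not confirmed by the study assay, "not fulfilling the 9vHPV 3-dose schedule", clearance by Month 7, and non-productive infection at baseline.

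The same 39 appears elsewhere as a recruitment figure. Section 1.1.6 says "A minimum of 39 and 30 subjects will be included in the RIFT-HPV 1 and 2 study cohorts respectively". Section 4.1 gives 39 and 30 as the minimum numbers who will enrol. Section 4.2.1 says "a minimum of 39 and 28 subjects for the first and second study cohorts respectively should be included in the study".

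For RIFT-HPV 2, section 9.2.2 does separate the two quantities: 28 women with anal infection are needed, and 30 are to be enrolled. Of those 30, 18 are expected to have anal infection, and 10 more such women are to come from RIFT-HPV 1. Section 9.1.1.2 plans a Wilcoxon signed rank test of Visit 1 against Visit 4, with the cervical samples analysed both jointly and by cohort.

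**The concern.** A number defined as women who completed the schedule cannot also be a number enrolled, when some of those enrolled are expected not to complete. Section 9.2.1 expects to lose 40%, yet the enrolment minimum equals the number needed after losses. If that is what was meant, the enrolment in 1.1.6 and 4.1 does not deliver the beta in 9.2.1 for the cohort being sized. A non-significant cervical result in RIFT-HPV 1 would then be read against 80% power that the cohort did not have. This is the comparison the protocol uses as the reference for sizing that cohort under the primary objective.

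**Working it through.** **Inputs.** Alpha 0.05 two-sided, power at least 80%, 39 completers, 25% reduction and 40% loss, all from 9.2.1. Enrolment of 39 and 30 from 1.1.6 and 4.1. Anal-infection expectations from 9.2.2. No SD, baseline mean or correlation is given.

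**Can 39 be reproduced?** No. With n = ((1.960 + 0.842) × SD / 0.25)², 39 pairs follow if the SD of the paired difference is about 0.56 (0.54 with the paired t). If 39 is instead the figure after dividing by 0.60, the SD would be about 0.43. Without a stated SD neither reading can be tested, so the standardised effect has to be solved back from 39.

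**Which reading do the other figures support?**
- Enrolment consistent with 39 evaluable: 39 / (1 − 0.40) = 65.
- Section 9.2.2 takes 10 anal cases from RIFT-HPV 1 at 28% or more. 0.28 × 39 = 10.9, while 0.28 × 65 = 18.2. So about 39 are enrolled, not 65.
- Evaluable women from 39 enrolled: 39 × 0.60 = 23.4.

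**Power in the RIFT-HPV 1 stratum.** The effect giving exactly 80% power at 39 pairs is d = 0.460 (paired t) or 0.449 (normal approximation). For the Wilcoxon test, simulated on normal differences, it is about 0.47. Holding that effect fixed:

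| Pairs | Paired t | Normal | Wilcoxon (simulated) |
|---|---|---|---|
| 23 | 56.0% | 57.6% | about 55.5% |
| 24 | 57.9% | 59.4% | about 57.7% |

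If the sponsor's calculation had rounding slack (the effect at which 38 pairs would just suffice, d = 0.467), the paired-t power at 23 pairs is 57%.

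**Detectable reduction.** At 23 pairs, 80% power needs d = 0.611. With the SD unchanged, 25% × 0.611 / 0.460 = 33%.

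**Joint cervical analysis (9.1.1.2).** Section 9.2.2 expects 18 of the 30 RIFT-HPV 2 women to have anal infection. The other 30 − 18 = 12 could qualify under 5.1 only through the cervix-positive branch. So, on the protocol's expectation, between 12 and 30 are cervix-positive. Assuming the same 40% loss in RIFT-HPV 2:
- Lower end: 0.60 × (39 + 12) = 30.6, about 30 pairs. Paired-t power at d = 0.460 is 68%.
- Upper end: 0.60 × (39 + 30) = 41.4, about 41 pairs. Power is 82%.

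**The case against.** The strongest reply is that 39 already contains the loss. 23 / 0.60 = 38.3, which rounds up to 39; sections 1.1.6 and 4.1 use 39 as enrolment; and the 10 anal cases fit 39 enrolled. Nothing in 9.2.1 says whether 39 is before or after losses. That stands as a possibility, so the loss of power is not a proven fact. It does not rescue the text, because 9.2.1 attaches 39 to women who completed three doses and non-completers are inside the 40%. Section 9.2.2 uses parallel wording for its 28, which is clearly the number needed, and then derives 30 to enrol. No such step is made for 39, and 4.2.1 pairs 39 with 28, not with 30.

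Three stronger inferences are tempting, and the documents do not support them.
- A reader might infer that 56% is the power of the cervical comparison as a whole. It is the power of one stratum; the joint analysis is also planned and would be larger.
- A reader might infer that all four losses are removed by the analysis-population rule in 9.1.1.1.2. That rule covers DNA, virions, exuded antibodies and seroconversion. It does not list schedule non-completion, and 7.1 and 8.1.9 keep discontinuers in follow-up. Such women fall outside the endpoint only because 9.1.1.1.1 refers to a three-dose regimen.
- A reader might infer from 5.3 ("A subject who discontinues from study vaccination or withdraws from the study will not be replaced") that no loss can be made good. It covers discontinuation and withdrawal only, and 39 is a minimum. No higher target is stated, however.

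In the other direction, 9.1.1.1.2 also excludes women without exuded antibodies or seroconversion, which the 40% list omits. So 23 pairs may be optimistic.

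**Conclusion.** Wrong as written. The same 39 is a number of completers in 9.2.1 and a number enrolled or included in 1.1.6, 4.1 and 4.2.1, with a 40% loss stated between the two and not visibly applied. On the literal text, the stated enrolment does not deliver the stated beta for RIFT-HPV 1: about 23 pairs, power about 56–58%, and about 33% detectable with 80% power. These figures rest on 39 pairs giving exactly 80% power, because no SD is stated; across the test approximations the range is about 55–59%. The joint cervical analysis would have about 68–82% power, further assuming the same loss in RIFT-HPV 2 and 12 to 30 cervix-positive women there. If 39 was meant to include the loss, the power figures do not follow, but the completer wording overstates the evaluable number by about 16 (39 − 23).

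**What to change.** In 9.2.1, 1.1.6, 4.1 and 4.2.1, state the enrolled and the evaluable number separately for RIFT-HPV 1. Give the SD or standardised effect behind the calculation. Then follow whichever case applies:

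- **39 is the evaluable requirement.** Restate the power for 39 enrolled: about 56% for the RIFT-HPV 1 stratum (recomputed from the actual SD), with the expected pairs and power of the joint cervical analysis beside it. If 80% power within RIFT-HPV 1 is to be kept, the consistent enrolment figure is 65.
- **39 already contains the loss.** Correct the wording that ties 39 to completed vaccination, and give the evaluable number, about 23, as the one the power refers to.

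Naming the joint analysis as the powered one and treating the cohort-specific cervical analyses as descriptive is optional.

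The cost is wording in four sections, the recovery of one input from the sponsor's calculation and, in the first case, a less favourable stated power. No extra patients are required unless the sponsor chooses to keep 39 evaluable.
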